### Plans to give access to the full protocol, participant level data and statistics code {31c}

Details of the full protocol, participant-level dataset, or the statistics code are not available to the public. Data not published may be made available upon reasonable request to the researchers responsible or corresponding authors of the publications.

## Oversight and monitoring

### Composition of the coordinating centre and trial steering committee {5d}

The university hospital serves as an administrative hub for the trial, hosting a central office with administrative staff. This central office coordinates the trial, monitors the trial progress and can aid all included study centres with administrative support during office hours. The trial is governed by a steering committee consisting of four researchers clinically active on the three initial study centres and an administrator. They will provide informational mailings to the responsible surgeon and administrative staff on all study centres twice a year and invite to an annual physical meeting.

### Composition of the data monitoring committee, its role and reporting structure {21a}

A safety analysis will be performed by an independent senior surgeon after 30 operations (more details under item 21b). This person will be certified to terminate inclusion in the study if undefendable differences between the treatment arms are found or if repeated method related severe adverse events are found in any of the study arms. If no such signs are found, results from the safety analysis will not be propagated to the steering board or participating centres. No other progressive data monitoring will be performed in this trial.

### Reporting adverse events and harm {22}

Adverse events and surgical complications are the main outcome of the trial and will be documented in the medical records. If they occur, they will be included in the CRF.

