The study intervention was developed with the aid of 3D-models reconstructed from computerised tomography (CT) scans of patients suffering from parastomal hernia. Four pilot patients have then been operated on in a feasibility study which showed no procedure-related complications [15].

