### Interim analyses {21b}

After 30 operations have been performed, a safety analysis is performed. It is conducted by a scientifically experienced researcher (at least assistant professor) with long clinical experience of abdominal wall surgery but has no connection with the study. The safety analysis is based on CRF data and complications graded Clavien-Dindo 3b or worse based on information from copies of the medical records from postoperative care on the ward and clinical follow-ups. Should serious or unexpected complications associated with study allocation arise, the study will be interrupted by the surgeon performing the safety analysis. Safety analysis data will otherwise not be available to the responsible researchers or surgeons participating in the study.

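### No stated route brings a severe adverse event to the one person with explicit stopping authority, except at the single analysis after 30 operations

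*Protocol article*

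**What the plan says.** Three sections of the protocol article bear on this.

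- **Timing.** Under Interim analyses {21b}: "After 30 operations have been performed, a safety analysis is performed". The data monitoring section {21a} agrees: "A safety analysis will be performed by an independent senior surgeon after 30 operations".
- **Authority and criterion.** Under {21a} this surgeon may end inclusion for indefensible differences between the arms, or "if repeated method related severe adverse events are found in any of the study arms". Under {21b}, if serious or unexpected complications linked to allocation arise, "the study will be interrupted by the surgeon performing the safety analysis". The material reviewed is CRF data and complications of Clavien-Dindo grade 3b or worse. No one else is given explicit power to stop.
- **Other monitoring.** {21a} states: "No other progressive data monitoring will be performed in this trial". The auditing section {23} plans nothing beyond the safety analysis.
- **Adverse event route.** Under {22}, adverse events and surgical complications "will be documented in the medical records. If they occur, they will be included in the CRF". No onward recipient and no time limit is given.

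On prior experience in this indication, the background {6a} says: "Four pilot patients have then been operated on in a feasibility study which showed no procedure-related complications".

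**The concern.** The criterion in {21a} concerns the recurrence of events, so it could be satisfied at any point in recruitment. The plan examines it when a set number of operations has been reached. Between the first operation and the thirtieth, the text describes no step that takes a severe event, or a cluster of them, to the person who holds the criterion. After the look, the same holds for the remaining 90 − 30 = 60 operations.

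Patient safety is at stake in the phase with the least evidence on this technique. Ward staff and the follow-up surgeon, who record much of the outcome data, are blinded ({17a}, {18a}). Deciding whether an event is related to the method or to the allocation requires the arm. The people best placed to notice an event are therefore not those who can classify it against the criterion.

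**Working it through.** **Passages side by side.** {21a} and {21b} place the criterion and the authority inside one analysis after 30 operations. {21a} excludes other progressive monitoring. {22} ends at the medical record and the CRF. {18a} has the ward CRF collected after discharge and entered in the database, with no forwarding step. Data management {19} gives the responsible researchers and administrators access to CRFs, and {5d} sets up a steering committee that governs the trial, but neither section assigns a safety review or a stopping rule. Read together, they contain no stated link between a severe event and the independent surgeon outside the planned analysis.

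**No figure to reproduce.** The number 30 is given without a calculation. What follows only shows scale.

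**What the pilot allows.** Input: 0 procedure-related complications in 4 patients ({6a}). The exact one-sided 95% upper limit is 1 − 0.05^(1/4) = 0.527. The two-sided limit is 1 − 0.025^(1/4) = 0.602. These limits refer to procedure-related complications, not to severe events specifically.

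**Patients per arm before the look.** Blocks of five with alternating majority ({16a}): 30 operations make 6 blocks, three with 3 and three with 2 in a given arm, so 3 × 3 + 3 × 2 = 15 per arm if envelopes are used in order.

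**Chance of at least two severe events in one arm.** The article gives no severe-event rate, so p is assumed. P(≥2) = 1 − (1 − p)^15 − 15p(1 − p)^14. For example, at p = 0.10: 1 − 0.2059 − 0.3432 = 0.451.

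The expected number of further patients in that arm operated on after the second event and before the look is Σ (15 − k)(k − 1)p²(1 − p)^(k−2) for k = 2 to 15. Dividing by P(≥2) conditions on a second event having occurred.

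| Assumed rate p | Expected events in 15 | P(≥2) in 15 | Further patients, given a second event |
|---|---|---|---|
| 5% | 0.75 | 17.1% | 0.85 / 0.171 ≈ 5.0 |
| 10% | 1.5 | 45.1% | 2.55 / 0.451 ≈ 5.7 |
| 20% | 3.0 | 83.3% | 6.01 / 0.833 ≈ 7.2 |
| 30% | 4.5 | 96.5% | 8.47 / 0.965 ≈ 8.8 |

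The last column assumes that an event is recognised before the next patient in the arm is operated on, so it is on the high side for late complications. If the arm has 12 or 18 patients at the look instead of 15, P(≥2) runs from 11.8% to 22.6% at p = 5%, 34.1% to 55.0% at 10%, 72.5% to 90.1% at 20%, and 91.5% to 98.6% at 30%.

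For context, Sample size {14} plans on short-term complication rates of 15% with the skin graft and 40% with mesh. Severe rates of 20% and 30% exceed the planning rate for the graft arm, so the 5% and 10% rows are closer to what the investigators expect there.

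**Calendar time.** 90 patients from December 2019 to December 2025 is 72 months. At an even pace, 30 operations take 72 / 90 × 30 = 24 months. Trial status reports that the pandemic prevented inclusion, so the look may come later.

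**The case against.** The strongest reply is that {22} is a two-sentence entry in a condensed article. It does not say that events go nowhere else, and the full protocol, which is not public ({31c}), may hold incident-reporting detail. The exclusion of further monitoring stands under the data monitoring heading and can be read as ruling out further scheduled looks, not the reporting of single events. This stands in part: absence of incident reporting cannot be proved from the article. However, the timing of the criterion and the exclusion of other progressive monitoring are positive statements, and an ongoing safety review elsewhere would contradict them.

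Three stronger readings are tempting, and the documents do not support them.

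- *Events reach nobody who could act.* The responsible researchers can open the CRFs ({19}), a steering committee of clinically active researchers governs the trial ({5d}), and there is a route for protocol changes ({25}). Those who run the trial may well learn of events. What is missing is a defined route to the one named decision-maker.
- *A second severe event meets the criterion, so the trial would continue in breach of its own rule.* The criterion requires that events be related to the method. That is a judgement, and two events do not settle it.
- *No one can see a pattern across centres.* The central office follows trial progress, a research nurse oversees the whole study population ({18b}), operating surgeons know the allocation, and a surgeon from an initial centre assists at the first operations in new centres ({11c}).

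It is also fair to say that the four pilot patients are not the only evidence. The background and discussion cite preclinical work and skin-graft repair of other hernias, described there as safe. The four patients are the experience reported for this technique in parastomal hernia.

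**Conclusion.** The point holds in a limited form. The only explicit stopping authority applies its criterion once, after 30 operations, and the article states no route or trigger by which a severe event reaches that person before or after. This rests on the article's own statements on timing and on other monitoring, together with the absence of any onward step in {22}.

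The size depends on a severe-event rate that the article does not give. At 5% in one arm the gap would seldom matter before the look (about one chance in six of two or more events). At 10% it is close to even, and at 20% or more two events are likely. Where a second event does occur, roughly 5 to 9 further patients in that arm would on average be operated on before the look. These figures assume 15 patients per arm, independent events and prompt recognition, and they count severe events without judging whether the method caused them.

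**What to change.** Reconcile {21a}, {21b} and {22} so that the reporting route matches the criterion:

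- Each centre reports every complication of Clavien-Dindo grade 3b or worse, the grade already used in {21b}, to the existing central office as it occurs. As recruitment began in December 2019, events already recorded should be sent at the same time.
- The central office forwards the report with the allocation to the independent surgeon, who applies the criterion already in {21a}. The article describes this person's qualifications but not an appointment, so the role should be confirmed as filled.
- The route stays open for the whole of recruitment. The analysis after 30 operations is unchanged, and results remain closed to the steering committee and centres as now planned.
- {21a} and {21b} describe the grounds and the consequence of a stop in different words (ending inclusion in one, interrupting the study in the other). The investigators should settle on one wording.

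No new committee and no new clinical threshold is introduced. If the full protocol already contains such a route, one sentence in {22} pointing to it is enough.

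The cost is a short amendment, a form or message per severe event, and a few case reviews. For the independent surgeon this turns a one-off task into a continuing one. There is no efficacy look, so no alpha is spent.

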### Frequency and plans for auditing trial conduct {23}

Other than the safety analysis, no other auditing is planned.

### Plans for communicating important protocol amendments to relevant parties (e.g. trial participants, ethics committees) {25}

Any protocol modification deemed necessary will first be reviewed by the Swedish Ethics Review Authority and then registered at ClinicalTrials.gov. This information will also be shared personally with the researcher responsible at each study centre.

### Dissemination plans {31a}

The results of the trial will be published in peer-reviewed open-access journals and presented at both national and international conferences.

## Discussion

Despite the relative frequency of parastomal hernia, there is a considerable lack of knowledge regarding epidemiology, symptomatology, indication for surgery and best practice when surgically managing the condition [1–3, 6]. The European Hernia Society guidelines on prevention and treatment of parastomal hernia provide predominantly weak evidence for both the epidemiological aspects of the disease and its subsequent treatment [16]. Since there is a general lack of studies comparing different techniques for parastomal hernia repair, there is no consensus on what the best method available is. This makes the design of a trial, and in particular, choosing a comparator to evaluate a novel treatment, difficult and even controversial. Our choice of using reinforcement with DynaMesh®-IPST as a comparator was made because of its similarity to our FTSG-method and with the background of recurrence rates in the vicinity of other IPOM methods [22]. Furthermore, recurrence of a parastomal hernia after surgical repair is of minor importance compared to the serious and sometimes fatal complications of repair methods using synthetic mesh as reinforcement. The primary goal of benign surgery must be the safety of the patients, which the primary outcome of this trial.

Both methods investigated in this trial are open techniques despite the increasing number of colorectal interventions being performed laparoscopically. This is primarily because it is not possible to apply an FTSG to the abdominal wall using conventional laparoscopic tacks. Therefore, to avoid cyst formation, an open technique with better control over the sutures was considered safer for the patients given the importance of the FTSG application under tension.

An advantage of using FTSG is that this reinforcement material is usually readily available in the quantity required. FTSG has been shown to be a safe and potentially useful alternative in giant incisional hernia repair [10, 23].

## Trial status

Current recruitment. The first patient was recruited December 2019. The global COVID-19 pandemic has unfortunately reduced resources available for major benign surgery and thereby prevented inclusion. Due to uncertainty about how the pandemic will affect the healthcare system in Sweden in the future, we cannot say when recruitment is likely to be completed. Our aim is to complete recruitment by December 31, 2025.

## Abbreviations

FTSG: Full-thickness skin graft
RCT: Randomised controlled trial
CRF: Case report form
VHPQ: Ventral hernia pain questionnaire
EORTC: European Organisation of Research and Treatment of Cancer
BMI: Body mass index
ASA: American Society of Anesthesiologists
IPOM: Intraperitoneal onlay mesh
QoL: Quality of life
